## Abstract

**Background:**

The influence of patients’ preoperative nutritional status on their clinical outcome has already been proven. Therefore, patients with malnutrition are in need of additional therapeutic efforts. However, for pancreatic surgery, evidence suggesting the adequacy of existing nutritional assessment scores to estimate malnutrition associated with postoperative outcome is limited.

**Objective:**

The aim of the observational trial “Nutritional Risk in Major Abdominal Surgery (NURIMAS) Pancreas” is to prospectively assess and analyze different nutritional assessment scores for their prognostic value on postoperative complications in patients undergoing pancreatic surgery.

**Methods:**

All patients scheduled to receive elective pancreatic surgery at the University Hospital of Heidelberg will be screened for eligibility. Preoperatively, 12 nutritional assessment scores will be collected and patients will be assigned either at risk or not at risk for malnutrition. The postoperative course will be followed prospectively and complications according to the Clavien-Dindo classification will be recorded. The prognostic value for complications will be evaluated for every score in a univariable and multivariable analysis corrected for known risk factors in pancreatic surgery.

**Results:**

Final data analysis is expected to be available during Spring 2016.

**Conclusions:**

The NURIMAS Pancreas trial is a monocentric, prospective, observational trial aiming to find the most predictive clinical nutritional assessment score for postoperative complications. Using the results of this protocol as a knowledge base, it is possible to conduct nutritional risk-guided intervention trials to prevent postoperative complications in the pancreatic surgical population.

**Trial Registration:**

germanctr.de: DRKS00006340; https://drks-neu.uniklinik-freiburg.de/drks_web/navigate.do?navigationId=trial.HTML&TRIAL_ID=DRKS00006340 (Archived by WebCite at http://www.webcitation.org/6bzXWSRYZ)

## Introduction

### Existing Evidence and Need for a Trial

Malnutrition is estimated as one of the leading causes for loss of health [1]. For hospitalized patients, the direct negative impact of malnutrition has broadly been examined [2-7]. Patients with tumorous diseases as well as patients being treated in intensive care units or in geriatric hospitals are mostly affected by negative impact of malnutrition [8-11].

To detect malnutrition, several scores have been developed. A recently published systematic review with meta-analysis investigated 32 scores with regard to their validity and predictive value for the population of hospitalized patients. The review indicated that only a small portion of scores had been fully validated and in particular, only limited scores are available for surgery. Development of new scores was considered redundant and they were not able to achieve higher sensitivity or specificity. Thus, trials investigating different scores in a specific patient population have been claimed necessary [12].

The population of surgical patients is specifically at high risk for being malnourished [13]. For some surgical indications, malnutrition has been proven as a risk of postoperative complications [14-16]. Regarding pancreatic surgery, limited data are available due to insufficient sample sizes or inhomogeneous populations. For example, the most recent pancreas-specific trial showed a correlation between the nutritional risk index and wound infections in patients after pancreaticoduodenectomy [17]. In addition, in this trial, the small sample size of 64 patients represents the major limitation.

### Aim of the Trial

“Nutritional Risk in Major Abdominal Surgery (NURIMAS) Pancreas” (DRKS00006340) is a monocentric, prospective, observational trial with one study arm. The aim of this trial is to find the best suitable clinical nutritional assessment score to predict postoperative complications in patients undergoing pancreatic surgery.

## Methods

### Study Population

The study population will comprise adult patients undergoing pancreatic surgery at the Department of General, Visceral and Transplantation Surgery at the University Hospital of Heidelberg. All underlying diseases leading to a primary pancreatic resection will be included. Thus, the analysis will give information on a broad and representative population as seen in high-volume surgical centers (Textbox 1).

Eligibility criteria.Inclusion criteriaAge ≥ 18 and ≤ 90 yearsElective pancreatic surgeryWritten informed consentExclusion criteriaAny former pancreatic-surgical proceduresLanguage problemsInability to understand the trial

### Diagnostic Intervention (Nutritional Assessment Scores)

Based on the most recent systematic review about existing nutritional assessment scores by Van Bokhorst-de van der Schueren [12], 11 scores have been selected that are in use in surgical patient populations [18-27]. Recently, the European Society of Clinical Nutrition and Metabolism (ESPEN) published a new consensus definition of malnutrition, the ESPEN malnutrition criteria [28]. Table 1 presents a summary of the 12 nutritional assessment scores that will be evaluated.

**Table 1 table1:** Nutritional assessment scores.

Name	Classification for nutritional risk^a^
Nutritional Risk Index [18]	Normal/mild/moderate/severe
Nutritional Risk Screening Score and Revised Version [19,26]	Low/ moderate/high
Subjective Global Assessment [20]	No/ moderate/severe
Malnutrition Universal Screening Tool [21]	Low/ medium/high
Mini-Nutritional Assessment and Revised Version [22,27]	Normal/ at risk/malnourished
Short Nutritional Assessment Questionnaire [23]	Low/ moderate/severe
Imperial Nutritional Screening System I [24]	Not at risk/at risk
Imperial Nutritional Screening System II [24]	Green/amber/red
Nutritional Risk Classification [25]	Low/at risk
ESPEN Malnutrition Criteria [28]	Normal/malnourished

^a^The highest class for nutritional risk determined by the scores will be used as the study end point “at risk for malnutrition” for statistical evaluation.

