### Trial Site and Sample Size Calculation

The trial will be conducted at the Department of General, Visceral and Transplantation Surgery at the University Hospital of Heidelberg. Prevalence of malnutrition in pancreatic cancer is known to be 88% [30]. We calculated sample size with a lower prevalence of 70% for all pancreatic diseases. With a specificity and sensitivity of 95% and a confidence interval of 0.05, a total of 260 patients will be needed [31]. Patients will be consecutively recruited until the study population will consist of 260 patients with major pancreatic resections (pancreaticoduodenectomy, distal pancreatic resection, or total pancreatectomy). Based on the department’s data (about 500 eligible pancreatic resections), recruitment will be completed within 12 months after inclusion of the first patient.

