### Statistical Analysis

The included scores use different numbers of nutritional risk classes. To compare the scores, evaluation of the primary end point patients will be dichotomized by each nutritional assessment score as “at risk” or “not at risk” using the respective highest nutritional risk determined by each score (Table 1). Further, patients will be dichotomized whether they had at least one major complication (Clavien-Dindo III-V) or not. Hence, for every nutritional assessment score, a contingency table will be created (Figure 1). Positive predictive value, specificity, sensitivity, and c-index will be calculated. Association between every nutritional assessment score and major complication will be expressed as odds ratio with 95% confidence interval. Univariable significance of association will be tested with a chi-square test without Yate’s correction at a level of significance of 5%. A multivariable logistic regression model will be used for evaluation of primary end point at a level of significance of 5%. Covariates will be age (years) and operation time (minutes). Factors will be malignancy; gender; laparoscopy; intraoperative radiotherapy; resection of vessels (portal vein, superior mesenteric artery, or vein); inclusion in an interventional trial; American Society of Anaesthesiologists (ASA) physical status classification system; prior upper gastrointestinal surgery; pancreatic surgery associated risks (amylase in drainage >5000 IE/U on POD 1, biliary stent); and preoperative serum albumin level less than 35 g/L. Subgroup analysis will be performed separately for different types of pancreatic resections and different nutritional risk classes will be determined by each score (Table 1).

Secondary end points will be analyzed descriptively by tabulation of the measures of the empirical distributions. According to the level of the variables, means, SDs, medians, 1st and 3rd quartiles, minimum and maximum, or absolute and relative frequencies will be reported, respectively. Descriptive *P* values of the corresponding statistical tests and associated 95% confidence intervals will be given. Statistical analysis will be performed with program R [43].

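### Each score is cut at its own highest class, so the ranking of scores mixes score quality with where the cut falls

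*Protocol article*

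**What the plan says.** The protocol article states the rule twice, and consistently. The footnote to Table 1 says "The highest class for nutritional risk determined by the scores will be used as the study end point" of being at risk for malnutrition. The Statistical Analysis section divides patients into at risk and not at risk "using the respective highest nutritional risk determined by each score", and gives the reason: "The included scores use different numbers of nutritional risk classes".

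Table 1 shows what this does:
- The Nutritional Risk Index has four classes, "Normal/mild/moderate/severe". Only *severe* counts.
- The Mini-Nutritional Assessment and its revision have three, "Normal/ at risk/malnourished". Only *malnourished* counts.
- The Imperial Nutritional Screening System II has three, "Green/amber/red". Only *red* counts.
- The Imperial System I, the Nutritional Risk Classification and the ESPEN criteria have two classes each, so any positive result counts.

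Under Outcome Measures, the most suitable score is the one with the highest lower 95% confidence bound of the odds ratio. The Statistical Analysis section also lists a c-index next to sensitivity and specificity from the 2x2 table, and a subgroup analysis by risk class.

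**The concern.** The trial exists to rank scores, so they should be compared on like terms. Here the same label covers different things. A patient whom the Mini-Nutritional Assessment itself calls at risk is analysed as not at risk. *Amber* on Imperial System II is a negative, while a plain at-risk result on System I is a positive. *Mild* and *moderate* on the Nutritional Risk Index join *normal*.

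The selection criterion adds to this. The lower bound of an odds ratio reflects precision as well as association, and precision depends on how many patients fall in the positive group. A score with a narrow top class can therefore rank low without being a worse score. The Discussion expects later intervention trials to rely on the result, so the choice of score matters beyond this study.

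**Working it through.** **Class counts (Table 1).** There are ten rows, and two of them also cover a revised version, which gives 12 scores. One has four classes. Eight have three: Nutritional Risk Screening and its revision, Subjective Global Assessment, Malnutrition Universal Screening Tool, Mini-Nutritional Assessment and its revision, Short Nutritional Assessment Questionnaire, and Imperial System II. Three have two. Check: 1 + 8 + 3 = 12. The rule merges an intermediate class into the negative group for 1 + 8 = 9 of 12.

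**Inputs.** N = 260 and the 95% level come from the protocol. It gives neither a major-complication rate nor any class frequency, so those below are assumptions. The plan has no figure for this comparison to reproduce.

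**Step 1: same true odds ratio, different share positive.** Let q be the share classed at risk and 30% the event rate. With odds ratio 2, the risks satisfy p1 = 2·p0/(1 + p0) and q·p1 + (1 − q)·p0 = 0.30. The lower bound is 2·exp(−1.96·SE), with SE = √(1/a + 1/b + 1/c + 1/d) over the four expected cells.

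| q | events / no events, at risk | events / no events, not at risk | SE | lower bound |
|---|---|---|---|---|
| 5% | 5.88 / 7.12 | 72.12 / 174.88 | 0.575 | 0.65 |
| 10% | 11.51 / 14.49 | 66.49 / 167.51 | 0.421 | 0.88 |
| 20% | 22.05 / 29.95 | 55.95 / 152.05 | 0.321 | 1.07 |
| 50% | 48.32 / 81.68 | 29.68 / 100.32 | 0.277 | 1.16 |
| 70% | 61.99 / 120.01 | 16.01 / 61.99 | 0.321 | 1.07 |

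From q = 5% to q = 50%, the bound goes from 0.60 to 1.07 at a 20% event rate, and from 0.65 to 1.21 at 40%.

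**Step 2: one identical underlying score, cut at different places.** Assume a log-odds slope of 0.4 per SD and 30% events. Cutting at the top 5, 20 or 50% gives odds ratios of 2.32, 1.97 and 1.88, lower bounds of 0.76, 1.05 and 1.09, and two-level c-indices of 0.522, 0.558 and 0.578. The narrowest cut has the largest odds ratio and the lowest bound.

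**Step 3: information lost by the top-class cut.** Assume 25% events, a log-odds slope of 0.8 per SD of latent nutrition, and a score sharing half its variance with that trait. Expected chi-square is 260·φ², and loss is 1 − (top class / trend).

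| Class split (%) | top class only | any risk | trend over classes | loss | c-index: top / any / all classes |
|---|---|---|---|---|---|
| 45/40/15 | 6.8 | 7.8 | 10.6 | 35% | 0.57 / 0.60 / 0.62 |
| 30/30/30/10 | 5.7 | 6.4 | 11.4 | 50% | 0.55 / 0.58 / 0.63 |
| 30/35/35 | 8.5 | 6.4 | 10.0 | 15% | 0.60 / 0.58 / 0.62 |
| 30/30/40 | 8.5 | 6.4 | 9.7 | 12% | 0.60 / 0.58 / 0.62 |

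Now let risk rise only in the top class: 45% there against 22% elsewhere, split 45/40/15. The order reverses, with chi-square 9.2 for the top class, 5.4 for trend and 1.3 for any risk. The expected c-index over all classes is then 0.577, the same as for the top class alone.

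**Step 4: the planned c-index.** Read in its place beside the 2x2 table, it is the c-index of a two-level variable, which equals (sensitivity + specificity)/2. In that form it repeats those two figures and inherits the same cut.

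**The case against.** The rule is prespecified, stated the same way in both places, and given a reason. Taking each tool's strongest category is a usable definition for selecting patients for later intervention trials, and the risk classes do get a subgroup analysis. All of this stands: it is a cut-off choice that is badly fixed for a comparison, not an inconsistency in the text. The subgroup analysis, however, sits outside the ranking and does not change which score is chosen.

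Four stronger readings are tempting, and the document does not support them.
- *The rule contradicts the planning prevalence.* The protocol says "We calculated sample size with a lower prevalence of 70% for all pancreatic diseases", but ties that figure to no score and no class. It is not shown to apply to a highest-class definition, and no more can be said.
- *A third to a half of the information is lost.* That needs small top classes. With top classes of 35-40% the loss is 12-15%, and if only the top class carries risk, the top-class cut is the better one.
- *The 2x2 cut should become any risk versus none.* That would put *mild* on the Nutritional Risk Index beside *malnourished* on the ESPEN criteria, so severity is still unequal, and it can be less informative (6.4 against 8.5 for the 30/35/35 split). An odds ratio per class step does not suit the selection criterion either. For the same underlying score it is about 1.65 with four classes (30/30/30/10), 1.9 with three (45/40/15) and 2.3 with two (50/50).
- *The chi-square test will have expected cells below 5.* At 20% events that needs fewer than 25 of the 260 patients in the top class (25 × 0.20 = 5), and the protocol gives no class sizes.

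**Conclusion.** The point holds in a limited form. Nine of the 12 scores are cut above at least one intermediate class and three are not. The class labels show that the cuts are not matched for severity; the number of classes alone would not prove it. Because scores are ranked on the lower bound of the odds ratio, cut placement alone can reorder them: 0.65 against 1.16 for the same true odds ratio of 2.0, at 5% and 50% positive with 30% events. Which scores gain or lose, and by how much, cannot be worked out from the protocol. Those figures rest on assumed event rates and class shares, and the information-loss figures also on the latent-trait model. In that model the c-index over all classes exceeded both two-level cuts in every split tried.

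**What to change.** Keep the highest-class 2x2 analysis and add three items to the Statistical Analysis section:
1. Compute the planned c-index over all published classes of each score, with a 95% confidence interval, and report it beside the odds-ratio ranking as the comparison that needs no added cut.
2. Repeat the odds-ratio ranking with any risk versus none as a prespecified sensitivity analysis. The results of the three two-class scores do not change; those of the other nine may.
3. State in advance that the choice of best score will be reported as cut-dependent if the rankings disagree.

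The cost is some extra analysis and text. No new data are needed, because the scores are already collected at Visit 1. One limitation should be stated: scores with more classes have more room to discriminate, which favours them on the c-index.

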### Outcome Measures

The primary end point is postoperative morbidity and mortality. The most suitable score is defined as the score with the highest association of malnutrition and postoperative complication expressed as the highest lower bound of the 95% confidence interval of odds ratio.

Secondary end points are length of hospital stay, length of stay in intensive care unit, comprehensive complication index [29], place of discharge (discharge to home or discharge to rehabilitation or care facility), necessity of postoperative parenteral or enteral nutrition, and impact of malnutrition as diagnosis on hospital costs and Diagnosis Related Group (DRG) case cost.

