## Discussion

The NURIMAS trial is a monocentric, prospective, observational trial aiming to find the most suitable clinical nutritional assessment score to predict major postoperative complications associated with malnutrition. Thus, an important lack of knowledge in preoperative risk assessment in patients undergoing pancreatic surgery will be worked-off. Upon this knowledge, further trials can rely on a validated nutritional risk and evaluate the benefit of nutritional interventions potentially preventing postoperative complications.

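### The rule for naming the best of 12 scores always yields a winner, treats the ranking as exact, and does not say which odds ratio is ranked

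*Protocol article*

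**What the plan says.** Outcome Measures in the protocol article defines the most suitable score as the one most strongly associated with complications, "expressed as the highest lower bound of the 95% confidence interval of odds ratio". No threshold or comparison between scores is attached.

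The Nutritional Assessment Scores section sets the number of candidates: "Table 1 presents a summary of the 12 nutritional assessment scores that will be evaluated". Under Statistical Analysis each score is cut in two "using the respective highest nutritional risk determined by each score", and patients are "dichotomized whether they had at least one major complication (Clavien-Dindo III-V) or not". Table 1 lists schemes with two, three or four classes, so the top class need not hold a similar share of patients from one score to the next.

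The same section supplies two candidate odds ratios. One comes from the contingency tables: "Association between every nutritional assessment score and major complication will be expressed as odds ratio with 95% confidence interval", with a chi-square test of each score at 5%. The other comes from a regression with many covariates: "A multivariable logistic regression model will be used for evaluation of primary end point at a level of significance of 5" per cent. Positive predictive value, sensitivity, specificity and c-index are also calculated but play no part in the selection.

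The Discussion expects that "further trials can rely on a validated nutritional risk" on the strength of this study.

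**The concern.** The selection rule produces the study's main conclusion, and the text leaves it open in three ways.

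- **No floor.** A largest value exists in any set of 12, so a score is declared most suitable whether or not any score predicts anything. The 5% test of each score is not made a condition for winning.
- **No statement of ranking uncertainty.** All 12 scores are measured in the same patients and their intervals will overlap, yet the order of the lower limits is read as exact. The largest of 12 noisy estimates is also biased upwards.
- **The ranked quantity is not identified.** The unadjusted odds ratio describes the score alone. The multivariable one conditions on, among other things, operation time and drain amylase on day 1 after surgery. The two can name different winners, so the primary conclusion could be settled after the data are seen.

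In addition, a lower confidence limit combines strength of association with precision, and precision depends on the share of patients a score flags. Later intervention trials are meant to build on the winner. An inflated odds ratio, or a near-tie reported as a clear result, would carry over into their design.

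**Working it through.** **The plan's own figure.** The article gives no calculation for ranking odds ratios. Its 260 comes from precision for sensitivity and specificity: 1.96² × 0.95 × 0.05 / 0.05² = 73; 73/0.3 = 244 for specificity, and 105 for sensitivity at 70% prevalence. With z = 2 the specificity figure is 254. So 260 is not reproduced exactly, but it is on the safe side and does not bear on this point. It is used below only as n.

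**Inputs.** From the article: n = 260, 12 scores, a 95% interval, 5% tests. Assumed, because the article does not give them: event rate (25%, or 20–40%), share flagged per score (5–70%), latent correlation between scores (0–0.7).

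**Step 1. Lower bound against share flagged.** For flagged share f, event rate e and odds ratio OR, solve f·p₁ + (1−f)·p₀ = e with odds(p₁) = OR × odds(p₀). This gives cells a, b (flagged with and without event) and c, d (not flagged with and without event). Then SE = √(1/a + 1/b + 1/c + 1/d) and L = exp(ln OR − 1.96·SE).

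With OR = 2.5, e = 25%, n = 260:

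| Flagged | a, b, c, d | SE | Expected L |
|---|---|---|---|
| 5% | 5.7, 7.3, 59.3, 187.7 | 0.578 | 0.81 |
| 10% | 11.1, 14.9, 53.9, 180.1 | 0.426 | 1.09 |
| 30% | 29.5, 48.5, 35.5, 146.5 | 0.299 | 1.39 |
| 50% | 43.3, 86.7, 21.7, 108.3 | 0.300 | 1.39 |

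The order can also change with n alone. OR 3 at 5% flagged against OR 2 at 40% flagged gives expected lower bounds of 0.97 v 1.13 at n = 260, and 2.10 v 1.67 at n = 2600. In simulation at n = 260 the OR 3 score loses in 61% of runs.

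**Step 2. No score predictive.** With independent scores, the chance that at least one lower bound exceeds 1 is 1 − 0.975¹² = 0.26. Simulations with correlated scores and mixed flagged shares give about 19–28%. The winner's median observed odds ratio is about 1.5–1.8. Its median lower bound is 0.79–0.88, so in the typical null trial the rule crowns a score whose interval includes 1.

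**Step 3. All scores equally good.** With a true odds ratio of 2 for all 12 (30% events, correlation 0.3–0.6), the winner's median observed odds ratio is 3.1–3.2. A score flagging 5% wins about 4% of the time and one flagging 30–60% about 10–12%, although none is better than another.

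**Step 4. One score clearly better.** With OR 3 against 1.5 for the other 11 (30% events, correlation 0.5), the better score wins in 30%, 56%, 80%, 87% and 89% of runs if it flags 5%, 10%, 20%, 30% and 50%.

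**The case against.** The strongest defence is that a lower-bound rule is meant to discount imprecise estimates. An odds ratio resting on 13 flagged patients (5% of 260) should be discounted, and the article does not suggest that any score flags so few. This stands in part. A reader might infer that the winner merely reflects how many patients a score flags, plus chance. Step 4 does not support that: a clearly better score flagging at least 20% wins 80–89% of the time. The distortion matters when the best score flags few patients or when the scores are similar.

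A reader might also take 1 − 0.95¹² = 46% as the false-positive rate of the conclusion. That figure describes the chi-square tests, which do not choose the winner; the relevant figure is the 19–28% in Step 2. Multiplicity handling may also sit in an analysis plan that is not shown, so its absence from an article is not the point. The selection rule itself is stated here.

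Ranking by c-index may look like the natural cure. It is not. For a dichotomised score the c-index is (sensitivity + specificity)/2, which also depends on the share flagged: 0.525, 0.547, 0.602 and 0.611 for the four rows in Step 1. In the contest of OR 3 at 5% against OR 2 at 40%, the OR 3 score loses about 90% of runs on c-index, against 61% on the lower bound.

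Finally, every odds ratio will be reported with its interval, so a winner with a lower bound below 1 would be visible. That is true, but the rule would still call it the most suitable score.

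**Conclusion.** The point holds as a should-fix. The article fixes a rule that cannot return the answer that no score is suitable, attaches no uncertainty to the ranking, and does not say which of two planned odds ratios is ranked. These three gaps follow from the text and need no assumption.

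Their size does rest on assumptions. With no predictive score, about 19–28% of trials would present a winner with a lower bound above 1, at a median observed odds ratio of about 1.5–1.8. The exact values move with the assumed flagged shares, event rates and correlations; the upward direction of the bias does not. The disadvantage for scores flagging about 10% or fewer is real at n = 260, but it does not make the rule blind to true association. Nothing in the planned analysis corrects for selection or tests the winner in other patients, so the Discussion's claim of a validated risk goes further than the design allows.

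**What to change.** Before the database is closed, the analysis plan should:

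1. State whether the unadjusted or the multivariable odds ratio decides, and report the other as supportive.
2. Call a score predictive only if its association holds after allowing for 12 scores, by Holm or a max-T permutation test, so that no suitable score is a possible result.
3. Bootstrap patients jointly over all 12 scores and repeat the selection in each resample. Report the winner's optimism-corrected odds ratio, paired 95% intervals for the winner against each other score, and each score's probability of ranking first.
4. Name a single best score only if the paired differences support it; otherwise report a leading group.

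The lower-bound ranking can stay as the descriptive order and should not be replaced by c-index ranking. The cost is wording and some R programming on data already being collected. The downside is that the trial may report several equally good scores, or none, in place of one winner.
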